## Abstract

**Introduction:**

Primary total elbow replacement (TER) services in England are being restructured with the goal of centralising care to specialised centres. It is important to monitor the impact of this service redesign. This protocol outlines an intended analysis to provide detailed descriptions of the patients who are receiving primary TER, where and by whom TER is being performed, and what the current surgical practices for TER are in England before the reconfiguration.

**Methods:**

This analysis will use the National Joint Registry (NJR) elbow dataset and link it with NHS England Hospital Episode Statistics-Admitted Patient Care (HES-APC). It will include eligible patients from the start of the NJR elbow dataset in April 2012 to December 2022. The main objective is to determine the incidence of TER in England. Age-sex standardised rates will be calculated for groups including different ethnicities, and socioeconomic backgrounds, using the mid-year population data provided by the Office for National Statistics. This planned analysis will summarise patient characteristics such as age, sex, body mass index (BMI), hand dominance, American Society of Anaesthesiologists (ASA) grade, indication for TER, socioeconomic status, and patient co-morbidities. It will also examine implant fixation type, classification, brand/type, and changes over time in implant types used in England. Additionally, it will explore the characteristics and volume of the surgeons and hospitals providing primary TER services, including the grade of the primary surgeons, funding source for surgery, and admission type. The analysis will cover the number of procedures performed by surgeons and hospitals annually in England and in each region of England. Finally, the planned analysis will summarise the elective wait time, postoperative length of stay, and any serious adverse events or re-admissions within 30 and 90 days after the TER.

**Discussion:**

This protocol describes the first deep dive analysis into the NJR elbow dataset to describe the incidence of TER surgery in England and the characteristics of patients who are receiving it. This analysis will summarise current primary TER practices in England before service reconfigurations. The impact of reconfiguration can be monitored by comparing future practice to the outcomes from this study.

*Trial registration* ClinicalTrials.gov, NCT06355011. Registered 02 April 2024, https://clinicaltrials.gov/ct2/show/NCT06355011.

**Supplementary Information:**

The online version contains supplementary material available at 10.1186/s13018-024-04903-9.

## Introduction

Total elbow replacement (TER) is an established treatment of painful elbow conditions including inflammatory arthritis, osteoarthritis, trauma sequalae, and in the treatment of complex distal humerus fractures [1]. Despite its established role, the number of TERs performed each year is much lower than other joint replacements such as hip, knee, and shoulder replacements [2]. In England and Wales, the number of TERs performed yearly between 2012 and 2022 ranged between 258 and 463 [2]. In 2018, the British Elbow and Shoulder Society (BESS) reported the average number of TERs performed per surgical unit to be two to three and that 73 surgeons performed one TER in 2016 [3]. This was a cause for concern, as there are studies in the lower limb and shoulder replacement surgery reporting higher volumes, by surgeons and hospitals, are associated with lower revision rates [4–8]. In addition, it has been reported that specialised centres and surgeons who perform a higher number of TERs have a lower risk of revision, although the quality of this evidence was judged to be very low in a recent systematic review [9–11].

In 2015, the Getting It Right First Time (GIRFT) national programme was introduced to improve medical care within the NHS by reducing unwarranted variations in outcomes [12]. GIRFT sought to rationalise the delivery of orthopaedic care within the NHS in England, addressing cost and efficiency. One aspect GIRFT targets is to centralise the provision of low volume procedures, such as TER, to specialised centres [12]. BESS and GIRFT have collaborated to produce guidelines and recommendations focused on the delivery of primary and revision elbow replacement [3]. Discussions have been held to reduce the number of centres providing primary and revision TER. The perceived benefit is to increase in the average number of TERs performed per surgeon and unit with concentration of resources, experience, and expertise, and to increase training opportunities to improve patient outcomes [12].

Whilst there are theoretical benefits to service changes, with some evidence from other countries that rationalisation of services can improve outcomes, it is important to monitor the effect of service redesign [13]. The purpose of this protocol is to outline the intended analysis of the TER procedures carried out in England, with a specific focus on (1) which patients are receiving TER surgery, (2) where and by whom TER surgery is undertaken, and (3) current surgical practices for TER, in England.

## Method and analysis

The findings and methodology of this study will be reported in accordance with the REporting of studies Conducted using Observational Routinely-collected health Data (RECORD) statement [14].

### Source of data

In this analysis data from the National Joint Registry (NJR) will be used. The primary purpose of NJR is to collect data on joint replacements to provide timely warnings of issues relating to patient safety [15]. In doing so, the NJR collects high-quality data that is commonly used in orthopaedic research [15]. The NJR elbow dataset will be the primary data source and it will be linked with data from the NHS England Hospital Episode Statistics-Admitted Patient Care (HES-APC) dataset to incorporate data that are not collected by the NJR.

The NJR started collecting elbow replacement procedures in April 2012. It is currently compulsory for all NHS and independent hospitals in England, Wales, Northern Ireland, the Isle of Man, and the States of Guernsey to submit elbow replacement surgery data, including primary and revision surgery, to the NJR [16]. The NJR collects data using a collection tool called the Minimum Data Set (MDS) form, which is usually filled out by a clinician at the time of surgery. Information regarding the implants used is usually completed by administration staff by including the implant codes (usually stickers that are attached to each implant) in the MDS form. All the information from the MDS forms is entered directly into the NJR data entry system locally by the hospital where the procedure was performed. When the NJR started collecting elbow replacement procedures in April 2012, version 5 of the MDS (MDSv5) was in use. The MDS has been updated twice to version 6 in November 2014 and version 7 in June 2018. Data collection using MDS version 8 started in June 2023, and the changes made in MDSv8 will not impact this project. The changes are summarised in Supplementary File 2.

There is currently a live automated data quality audit process to address any potential missing procedures, which started in June 2020 [17]. A collaborative audit between the NJR, British Orthopaedic Trainee Association (BOTA), British Orthopaedic Association (BOA), BESS and The Royal College of Surgeons of England (RCSEng) showed the completeness of the TER dataset to be 93% and the accuracy to be 98%. This audit included all TER procedures from the start of data collection in April 2012 until the live automated audit started. High completeness of the target population limits selection bias and increases the generalisability of results [18].

The HES-APC dataset contains details about inpatient admissions funded by the NHS, including patients in independent hospitals funded by NHS trusts. All patients undergoing TER surgery are admitted to hospital, and their data will be included in the HES-APC. Each NHS trust collects data while the patient receives treatment. The data are usually collated locally by clinical coders using the patient medical records and then submitted to NHS England. Once collated, NHS England processes and assesses the quality of the data and the yearly HES datasets are released for secondary use, including research. HES includes demographic, clinical, and administrative information which can be used to assess the practices and trends of joint replacement surgery. These include information such as co-morbidities, socioeconomic status, length of hospital stay, and ethnicity [19].

The data linkage of HES-APC to the NJR will be performed as part of an existing agreement between the NJR and NHS England. Access to the data is facilitated under NJR permissions. The data linkage will be performed by applying seven linkage methods using a combination of matched NHS numbers, Local patient ID, date of birth, year of birth, gender, and/or matched care provider (Supplementary File 1). Procedures that are matched based any of those linkage methods will be included, but for a procedure to match, the HES-APC hospital episode start date must be the same or before the NJR operation date whilst the NJR operation date must be before or the same as the HES-APC episode end date.

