### Participants

All patients aged 18–100 years old with a primary TER on the NJR elbow dataset from the start of data collection on the 1st of April 2012 to the 31st of December 2022 will be included. Patients are excluded if they did not consent for their data to be used for research purposes, if it is impossible to trace them after surgery, if their ID numbers are invalid, or if the surgery was not performed in England. Several steps will be undertaken to confirm that the included cases are primary TER procedures. This will include (1) ensuring all operative patterns are consistent (2) confirming all reported procedures on the NJR matches the implant components submitted. Unconfirmed procedures and procedures with inconsistent operative patterns (i.e. a sequence of operations where the primary operation is not the first operation in the sequence or where there are multiple primary operations recorded for the same joint) will be excluded from the analyses. The data preparation process and exclusion of non-eligible procedures is summarised in Fig. 1. Eligible NJR procedures will then be linked to the available HES-APC data which includes all patients’ hospital episodes from 23rd of October 1996 to 31st of March 2022. Hospital episodes with invalid ID numbers, implausible dates, unknown discharges dates, and duplicate episodes will be excluded (Fig. 2).

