#### Surgeon and hospital related factors

Most of the surgeon and hospital variables used in this study are not directly reported but will be derived from the available data (Table 3). The NJR includes pseudonymised codes to represent the surgeon who performed the surgery and the hospital where the surgery was performed. This data can be used to calculate the surgeon’s and hospital’s volume. In this project, the annual number of TERs will include all TERs from the 1st of January to the 31st of January of that year. The year 2012 will be excluded from this analysis because data is only available from April 2012.

**Table 3 Tab3:** Surgeon and hospital related variables to be included in the planned study

Variable	Dataset	How will data be presented	Method of measurement
Funding	NJR	Categorical: NHS/Independent sector	Documented directly using a specified list on MDS collection form
Grade of primary surgeon	NJR	Categorical: Consultant/Other	Documented directly using a specified list on MDS collection form
Surgeon volume	NJR	Number of TERs performed by a surgeon per year by surgeons	Derived from pseudonymised codes representing the surgeon in charge of patient care. It represents the number of TERs performed from 1st of January to the 31st of December of each year
Hospital volume	NJR	Number of TERs performed by a hospital per year by surgeons	Derived from pseudonymised codes representing the hospital where TER was performed It represents the number of TERs performed from 1st of January to the 31st of December of each year
Regional volume	NJR	Number of TERs per year by surgeons by region	Derived from the hospital where TER was performed. It represents the number of TERs performed from 1st of January to the 31st of December of each year
Duration of elective wait	HES	Number of days waiting	Derived from the date which it was decided to admit the patient and actual admission date
Post-operative duration of stay	HES	Number of inpatient days following surgery	Derived from the date of surgery and date of discharge
Elective admission type	HES	Categorical: General admission/Day case admission	Documented in patient medical records

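### HES-APC is said to hold every TER patient, but by the protocol's own definition it holds NHS-funded admissions only, so HES-derived results describe NHS-funded linked TER rather than all TER in England.

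*Protocol article*

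**What the plan says.** Source of data describes the linked dataset in two adjacent sentences. The first defines its scope: "The HES-APC dataset contains details about inpatient admissions funded by the NHS, including patients in independent hospitals funded by NHS trusts". The second claims full coverage: "All patients undergoing TER surgery are admitted to hospital, and their data will be included in the HES-APC".

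The cohort comes from the National Joint Registry (NJR), which is wider. On submission to the NJR the same section says: "It is currently compulsory for all NHS and independent hospitals in England, Wales, Northern Ireland, the Isle of Man, and the States of Guernsey". The Participants section excludes for consent, tracing, invalid identifiers and surgery outside England, among other checks ("Patients are excluded if they did not consent for their data to be used for research purposes, if it is impossible to trace them"), but not for funding. Table 3 lists Funding as "Categorical: NHS/Independent sector". The Abstract treats this as a description of who pays: "including the grade of the primary surgeons, funding source for surgery, and admission type".

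The linked data supply elective wait and post-operative stay (both secondary outcomes), day-case status, co-morbidities and both Charlson indices, ethnicity, and serious adverse events at 30 and 90 days. They also decide whether an Essex Lopresti injury counts as acute or chronic. The Abstract states that "the planned analysis will summarise the elective wait time, postoperative length of stay" will be reported, and the Discussion describes the study as a summary of practice in England before reconfiguration. The only HES limitation named there is extraction from unstructured paper records.

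**The concern.** The two sentences can both be true only if every TER in the cohort is NHS-funded, and the protocol does not assume that. A reader who accepts the second sentence will take the HES-derived results as covering all TER in England, and will put any unlinked procedure down to imperfect matching.

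Two things are at stake. The first is scope: the study is meant as a baseline for judging service reconfiguration, and a later comparison needs to know which population the waits, stays and adverse events refer to. The second is the ethnic-group rates. Their numerator needs ethnicity from HES, while their denominator is the ONS population of each group, whoever pays for surgery. Cases without ethnicity leave the numerator but not the denominator.

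**Working it through.** **1. Can a non-NHS-funded procedure enter the linked set?** A match requires an episode that spans the operation: "the HES-APC hospital episode start date must be the same or before the NJR operation date", and the operation must not fall after the episode ends. By the protocol's definition, a TER not funded by the NHS has no such episode. Such procedures are eligible for the NJR cohort, since there is no funding exclusion, yet they cannot be matched. The coverage sentence is therefore wrong on the document's own terms.

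**2. Which results are touched?** Those listed above as HES-derived. Counts, overall rates, and surgeon, hospital and implant results come from the NJR and are not touched.

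**3. How large is it?** The protocol gives no non-NHS share, so there is no figure to reproduce. For illustration I assume a share f of 1%, 5% or 10%. The annual count of 258 to 463 is from the Introduction; it covers England and Wales, so it is somewhat too high for England.

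- Procedures a year without an index HES record: f × 258 to f × 463.
- If a proportion p is seen in linked procedures, the all-England proportion lies between p(1 − f) and p(1 − f) + f. I take p = 5% day cases, also an assumption.
- The all-England median lies between the linked-set quantiles (0.5 − f)/(1 − f) and 0.5/(1 − f).

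| f | Procedures a year | Proportion, linked p = 5% | Median lies between linked-set quantiles |
|---|---|---|---|
| 1% | 2.6 to 4.6 | 4.95% to 5.95% | 49.5% and 50.5% |
| 5% | 12.9 to 23.2 | 4.75% to 9.75% | 47.4% and 52.6% |
| 10% | 25.8 to 46.3 | 4.5% to 14.5% | 44.4% and 55.6% |

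These are worst-case bounds on the funding gap alone. Medians move little. A small proportion could move more, but its upper bound requires every missing patient to be a day case.

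**4. Ethnic-group rates.** If a share f of a group's procedures has no ethnicity, its rate is multiplied by 1 − f, that is 0.99, 0.95 or 0.90 for the three values. Patient related variables allows ethnicity to be taken from a patient's other admissions, which may recover some cases. Whether that extends to patients whose TER itself is unlinked is not stated.

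**5. A second reason procedures cannot link.** Participants runs the NJR cohort from 1 April 2012 to 31 December 2022 (129 months) but ends the HES data on 31 March 2022. The last 9 months have no HES data: 9/129 = 7.0% of the period. This is separate from funding, but any count of unlinked procedures has to allow for it.

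**The case against.** The best defence is that the funding limit is disclosed in the preceding sentence, and that the second sentence only explains why an admitted-patient dataset suits TER. The reconfiguration concerns NHS care, so NHS-funded waits and stays are largely the baseline needed. Funding is a planned variable, and the analyses are repeated by year, so the non-NHS share and any drift in it should be visible. That much stands, and it keeps the point modest. It does not rescue a sentence that says all patients, which nothing later corrects.

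Several stronger readings are tempting but not supported:

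- *Every HES-derived proportion is too low by the non-NHS share.* This would need all NJR procedures as the denominator. The protocol does not set one; it says matched procedures will be included, and it has a separate flow diagram for the linked data. With a linked denominator the issue is scope, not understatement. The ethnic-group rates are the exception, because their denominator is fixed by population.
- *The linkage rate will be misreported.* No linkage rate is announced, and unlinked procedures are nowhere called failures. Fig. 2 and Supplementary File 1 are not available here. A ceiling calculated from funding alone would also be wrong. With an assumed share of 3% to 10% it gives 97% to 90%. Allowing for the HES end date, with even volume, gives about 0.93 × 0.97 = 90% to 0.93 × 0.90 = 84%.
- *Privately funded patients wait less and are healthier, so the direction of bias is known.* The document has nothing on this.

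The level named Independent sector could also denote provider rather than payer. The variable name and the Abstract point to payer, but this should be confirmed before the field is used to classify unlinked procedures.

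**Conclusion.** The coverage statement is wrong as written. HES-derived results describe NHS-funded, HES-linked procedures, while the article presents them as TER in England. This follows from the text alone and needs no assumed figure.

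The size of the effect cannot be determined from the document. Over an assumed non-NHS share of 1% to 10% it is probably small for medians and uncertain for small proportions, and it lowers ethnic-group rates to the extent that ethnicity is missing. A reader might infer that the incidence of TER is also affected. Apart from the ethnic-group rates it is not, because overall counts and rates rest on the NJR. The point is worth correcting because the study is intended as a reference baseline and the correction is nearly free.

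**What to change.** - Correct the sentence in Source of data so that it says HES-APC covers NHS-funded TER, and add this to the limitations.
- In Outcome and Statistical analyses, state that HES-derived items use HES-linked procedures as the denominator, within the period HES covers (to 31 March 2022). Label them as NHS-funded TER in England.
- Report the number of unlinked procedures by NJR funding source, after confirming that the field records payer and not provider. Separate procedures that cannot link (non-NHS-funded, or after 31 March 2022) from failed links.
- For ethnic-group rates, report how many procedures have no ethnicity and state that the rates are understated to that extent, or restrict their stated scope to NHS-funded TER.

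The cost is some wording and one tabulation on a variable already collected. The downside is a narrower stated scope for the HES-derived outcomes.

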### Patient and public involvement

The Patient and Public Involvement and Engagement (PPIE) members at Wrightington hospital were consulted and involved in the study objectives and methodology.

### Ethics

The NJR Research Committee approved this study [20]. The NJR supports public health surveillance and wider clinical decision-making and holds pseudonymised data that are anonymous to the researchers who use it. The NHS Health Research Authority tool guidance dictates that the secondary use of such data for research does not require approval by a research ethics committee [21]. Patients consented to inclusion in the NJR according to standard practice, with permission under the Health Service (Control of Patient Information) Regulations, otherwise referred to as Section 251 support [22].

### Participants

All patients aged 18–100 years old with a primary TER on the NJR elbow dataset from the start of data collection on the 1st of April 2012 to the 31st of December 2022 will be included. Patients are excluded if they did not consent for their data to be used for research purposes, if it is impossible to trace them after surgery, if their ID numbers are invalid, or if the surgery was not performed in England. Several steps will be undertaken to confirm that the included cases are primary TER procedures. This will include (1) ensuring all operative patterns are consistent (2) confirming all reported procedures on the NJR matches the implant components submitted. Unconfirmed procedures and procedures with inconsistent operative patterns (i.e. a sequence of operations where the primary operation is not the first operation in the sequence or where there are multiple primary operations recorded for the same joint) will be excluded from the analyses. The data preparation process and exclusion of non-eligible procedures is summarised in Fig. 1. Eligible NJR procedures will then be linked to the available HES-APC data which includes all patients’ hospital episodes from 23rd of October 1996 to 31st of March 2022. Hospital episodes with invalid ID numbers, implausible dates, unknown discharges dates, and duplicate episodes will be excluded (Fig. 2).

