### Outcome

The primary outcome in this proposed study will be the number and/or the rate of provision of primary TER. Secondary outcomes will include the duration of elective wait and post-operative duration of stay measured in days. Current trends will be described by reporting the outcomes on annual basis.

Serious adverse events (SAE) within 30 days and 90 days from the index TER will also be reported. SAE will be defined as any severe medical complications leading to hospital admission, including pulmonary embolism, myocardial infarction, lower respiratory tract infection, acute kidney injury, urinary tract infection, cerebrovascular events, and all-cause death. SAE will be extracted from the HES-APC data and identified using ICD-10 codes.

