### Statistical analyses

Descriptive analysis will be performed for all included variables. Frequencies and proportion will be used to summarize categorical variables. The distribution of continuous variables will be assessed using histograms. It is likely that some of the continuous data, such as surgeons’ and hospitals’ volume, will be skewed, therefore, continuous variables will be reported using the median and interquartile range (IQR). The analyses will include summary of all the included population, stratified analysis for elective and acute trauma population, and analysis for each year from 2012 to 2022. The number of procedures performed by surgeons and hospitals will be summarised for the whole population and for each region in England and the results will also be reported on annual basis.

TER rates for different sexes, age categories, socioeconomic status categories and different ethnic groups will be reported. The rates of primary TER per 100,000 persons will be calculated by dividing the number of procedures in the NJR elbow dataset by the corresponding mid-year population estimates published by the Office for National Statistic (ONS). Sensitivity analysis will be performed using the census estimate from 2021. The population estimates by ethnic group reported by ONS will be used to estimate the rates of TER between different ethnicity groups. Age and sex standardised TER rates for each IMD group will be reported. Statistical analyses will be performed using Stata version 18 (StataCorp LP, USA).

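### HES-APC data end on 31 March 2022 but the cohort runs to 31 December 2022, and no separate end date is set for the HES-derived annual results and the 30/90-day SAE

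*Protocol article*

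**What the plan says.** Under Participants, patients with a primary TER "from the start of data collection on the 1st of April 2012 to the 31st of December 2022 will be included". The same section then links eligible procedures to the available HES-APC data, which hold "hospital episodes from 23rd of October 1996 to 31st of March 2022".

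Under Source of data, a match requires the HES episode to start on or before the operation date, and "the NJR operation date must be before or the same as the HES-APC episode end date".

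Under Outcome, the secondary outcomes are elective wait and post-operative stay, both taken from HES-APC (Table 3), and outcomes are to be reported annually. The section adds: "Serious adverse events (SAE) within 30 days and 90 days from the index TER will also be reported". On their source it says: "SAE will be extracted from the HES-APC data and identified using ICD-10 codes".

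Under Statistical analyses, the plan includes "analysis for each year from 2012 to 2022". Rates by ethnic group use ONS population estimates as the denominator. Table 1 gives HES as the source of ethnicity and co-morbidities.

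The text gives no earlier end date for HES-derived items and no rule for operations without full 30- or 90-day HES cover. The Discussion does not list the gap as a limitation.

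**The concern.** The article fixes the cohort dates, the HES dates, the linkage rule and the reporting years, and together these do not fit. For the last nine months of the cohort there is no HES episode to link to. For the three months before that, patients link but their follow-up is cut short.

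The study is meant as a baseline against which practice after reconfiguration will be compared. If the 2022 SAE row is too low because events after 31 March 2022 are not in the data, later practice could look worse than it is. If 2022 waits, stays and ethnicity-specific rates describe one quarter but carry a full-year label, the end of each trend is not comparable with the years before it.

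The authors already apply the right logic at the other end of the window. Under Surgeon and hospital related factors, 2012 is dropped from the volume analysis because data start only in April. No matching rule exists for the HES-covered part of 2022.

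**Working it through.** The plan states no figure for this gap, so there is none to reproduce. The check is calendar arithmetic on the protocol's own dates.

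**Inputs**
- Cohort: 1 April 2012 to 31 December 2022 (Participants).
- End of HES: 31 March 2022 (Participants).
- SAE windows: 30 and 90 days (Outcome).
- Yearly TERs: 258 to 463 (Introduction). This range is for England and Wales, so it overstates England and is used only for illustration.

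**Coverage**
- Cohort length: 3,927 days. Days after HES ends: 275, and 275/3,927 = 7.0%.
- Linkable period: 3,927 − 275 = 3,652 days.
- Calendar 2022: 90 of 365 days covered (24.7%), 275 not covered (75.3%).
- Procedures with no HES cover, if spread evenly: 258 × 275/365 ≈ 194 to 463 × 275/365 ≈ 349.

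**Last operation date with full follow-up**
- 90-day: 31 March 2022 − 90 days = 31 December 2021. No 2022 operation qualifies. The linkable January-March 2022 procedures number about 258 × 90/365 ≈ 64 to 463 × 90/365 ≈ 114.
- 30-day: 31 March 2022 − 30 days = 1 March 2022. Operations on 2-31 March fall short, about 258 × 30/365 ≈ 21 to 463 × 30/365 ≈ 38.

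**Effect on SAE rates.** Assumptions: operation dates uniform, event times uniform within the window, only linkable procedures in the denominator.
- 90-day, 2022 row: remaining follow-up runs from 0 to 89 days, mean 44.5. Captured share is 44.5/90 = 49.4%, so the shortfall is about 51%.
- 90-day, pooled: 90 × (1 − 0.494) = 45.5 operation-days' worth of events are lost, and 45.5/3,652 = 1.2%.
- 30-day, 2022 row: 60 days are fully followed. The last 30 have 0 to 29 days, mean 14.5. Captured share is (60 + 30 × 14.5/30)/90 = 74.5/90 = 82.8%, so the shortfall is about 17%.
- 30-day, pooled: 15.5/3,652 = 0.4%.

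**Which items depend on HES**
- Not affected (NJR): number and rate of TER overall; rates by age, sex and IMD; implant variables; surgeon, hospital and regional volume.
- Affected for 2022 (HES): elective wait, post-operative stay, elective admission type, co-morbidities, ethnicity-specific rates and SAE.
- For ethnicity-specific rates, if only linked procedures are counted, the 2022 numerator covers 90 of 365 days, about a quarter of the year, against a full-year population.

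**The case against.** The strongest reply is that the HES end date is disclosed, that the protocol has separate flow diagrams for the unlinked and the linked dataset, and that the linkage rule itself ends the linked set at 31 March 2022. A condensed article may leave date filters to the analysis plan, and the linked flow diagram, which is not shown, may carry a cut-off. The study is descriptive, so no test or sample size depends on this.

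Much of that stands, and it limits the point. Four stronger readings that a reader might infer are not supported:

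- *The primary outcome is truncated.* It is not. Counts and rates divide NJR procedures by population estimates, and only the ethnicity breakdown needs HES.
- *The 194 to 349 later procedures count as event-free.* They cannot link, so they leave the HES tables. They would bias SAE rates only if kept in the denominator, which the protocol does not say. In that case the pooled shortfall would be 1 − (3,652 − 45.5)/3,927 = 8.2% at 90 days and 1 − (3,652 − 15.5)/3,927 = 7.4% at 30 days, so the denominator should be stated.
- *All early-2022 patients are unobserved at 30 and 90 days.* Operations from 1 January to 1 March 2022 have full 30-day follow-up, and partly followed patients still contribute events recorded by 31 March.
- *2022 is the most important baseline year.* The protocol gives no reconfiguration date and does not rank the years.

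The protocol also allows missing ethnicity to be taken from a patient's other episodes, so the three-month numerator is a risk and not a stated plan. It is avoided only if unmatched patients are retained and have earlier HES records.

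What the reply does not remove is the commitment to results for each year to 2022, which is unqualified for HES items and cannot be met with the HES data described.

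**Conclusion.** The point holds for HES-derived results only and should be fixed. As written, 2022 figures for wait, stay, admission type and co-morbidity would describe January to March. The 2022 ethnicity-specific rates risk a mismatch of numerator and denominator. The 2022 SAE row would be too low, by about 51% at 90 days and 17% at 30 days.

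The pooled 2012-2022 SAE rates would be too low by only about 1.2% and 0.4%, relative. These percentages rest on uniform operation dates and event times and on a denominator of linkable procedures. If events cluster soon after surgery, the shortfall would be smaller. The cut-off dates rest on no assumption beyond the protocol's own dates.

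**What to change.** State an end date for each group of outcomes:

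- NJR-only outcomes: keep 31 December 2022.
- 90-day SAE: operations up to 31 December 2021, with linked procedures only as the denominator.
- 30-day SAE: operations up to 1 March 2022, with the same denominator rule and any 2022 row labelled as a part year.
- Other HES-derived variables and ethnicity-specific rates: end the annual tables at 2021, or label 2022 as January to March and use a matched part-year denominator for the rates.

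State also whether procedures without a matching index episode can take ethnicity from earlier episodes. The alternative is to obtain HES-APC to at least 31 March 2023 (31 December 2022 + 90 days) and keep one window.

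The first option costs a few sentences and a date filter. About 64 to 114 linkable January-March 2022 procedures would leave the 90-day SAE table, and about 21 to 38 the 30-day table. Both ranges overstate England, because they come from England-and-Wales counts. The procedures after 31 March 2022 are no extra loss for index-admission items, since they cannot link anyway. The second option needs a further data release.
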